**Fig. 1 Fig1:**
[figure not shown]
Shows the flow chart for the randomized control trial program. TAM– Total Active movement, FDS– flexor digitorum superficialis

### Study population

All patients aged 18–65 years qualifying for the inclusion criteria (vide infra) are considered for the trial. Comprehensive information encompassing enrollment, details of the surgery, plan of immobilization, associated benefits, risks, and complications, type of rehabilitation protocol, methods of evaluation during the follow-up, and assigned person of contact for queries and emergency events will be provided. The patient’s privacy will be protected, and those unwilling to continue the trial program will be allowed to exit the study unconditionally. Patients will be informed that they will be included in the active or passive flexion mobilization regime. Patients will be counseled to provide written informed consent.

**Inclusion criteria**:

Age group: 18–65 years.Any of Grade 1/ 2/ 3 of the Defined Spaghetti Wrist as suggested by Koshy et al. [3]

**Exclusion criteria**:

Associated hand/ wrist fractures.The active movement of the digit is preserved at IP joints (Only one flexor tendon for finger or partial injury not requiring four-strand Kessler repair).Polytrauma.Patient unable to attend hand therapy program.

### Randomization and blinding

Forty-four patients who fulfill the study’s inclusion criteria and have signed the informed consent form will be randomly assigned in a 1:1 ratio of 22 each, using block randomization for either the early active motion group or the passive motion group. This block randomization will be created using a computer-generated randomized controlled table. Randomization will be done 24 h before the surgery. An opaque sealed envelope with sequential numbers will hold the allocation sequence. The sole information on this envelope’s label will be its unique ID number, which is numbered progressively and includes study details. To ensure a blind and identical appearance at the time before surgery, an independent resident not involved in the treatment will receive the envelope. They will then prepare the patient for an active or passive flexion mobilization program (Table 1). The active versus passive mobilization protocol is tabulated in Table 1. The surgeons, hand therapists, and data assessors tracking the patients are thus blinded by this approach, which will be maintained until the end of the trial period.

**Table 1 Tab1:** Table showing the regime followed for the early active and the passive mobilization groups

Weeks	Early protected active	Passive mobilization
5th day	Dorsal thermoplastic splint with wrist 10^0^ flexion, MCP 40^0^ flexion, and IP full extension (Wrist immobilized till 6 weeks)	Dorsal thermoplastic splint with wrist 10^0^ flexion, MCP 40^0^ flexion, and IP full extension. (Wrist immobilized till 6 weeks)
Day 5–12	25% excursion (active flexion) of the affected digits at IP and MP joints (Remove the Velcro strap at the digital and palmar level) The patient is instructed to flex only 25% of the range possible and extend the fingers until full extension at IP joints within the splint. (20 repetitions/10 times a day of active flexion and extension exercise per hour)	Full passive flexion of the affected digits at IP and MP joints (Remove Velcro strap at digital and palmar level) The patient is instructed to flex the finger passively with the other hand. Fingers actively extended within the splint as far as possible. (20 repetitions/10 times a day of passive flexion and active extension exercise per hour)
Day 12–21	50% excursion (active flexion) of the affected digits at IP and MP joints. (Remove the Velcro strap at the digital and palmar levels) The patient is instructed to flex only 50% of the range possible and extend the fingers until full extension at IP joints within the splint. (40 repetitions/ a day of active flexion and extension exercise) Ultrasound scar massage Tendon mobilization/gliding exercise and full ROM exercise started at 3 weeks.	Full passive flexion of the affected digits at IP and MP joints (Remove the Velcro strap at the digital and palmar levels) Flex the finger passively with the other hand. Fingers actively extended within the splint as far as possible. (40 repetitions/ a day of passive flexion and active extension exercise) Ultrasound scar massage Tendon mobilization/gliding exercise and whole ROM exercise started at 3 weeks.
Week 3–5	Splint modification - wrist brought to the neutral position. Remove the splint hol, d the wrist in neutral with the other hand, and encourage full active motion flexion and extension of IP and MP joints. Reapply the splint after exercise therapy. For the passive mobilization group, passive full flexion and active hold are started, followed by full active movement of flexion and extension as the weeks progress. (20 repetitions/ 10 times a day of active flexion and extension exercise per hour) At the end of the fourth week, full active motion range should be the goal (full extension at IP and MP joints) Low-intensity ultrasound scar massage (with intensities of 1 MHz, pulsed, 0.5 W cm-2) will be applied. Electrical stimulation of muscles in the hand for neurotmesis of the ulnar or median nerve (hypothenar/ thenar/ dorsal side for interossei) will be performed. Current type - Galvanic current () / Pulsed alternating current (AC) after re-innervation Pulse/cycle duration - >100 ms (GC) or 0.1-1 ms (Faradic current) Amplitude– as tolerated by the patient or till visible contraction observed Duration − 3 cycles of 30-30-30 contractions (Galvanic current), < 30 s (AC) Session frequency − 3–5 times/week, for 8–12 weeks approximately [16]	
Week 6	Wrist mobilization and electrical stimulation of long flexors, thenar, and hypothenar are started. Progression to full range of movements of wrist and fingers	
Week 8	Blocking and light resistance exercises, full resistance is prohibited, splint is removed and worn only at night. Activities of daily living (ADL) are not yet advised. Introduction of the static splinting program to get at the interphalangeal joint (IP) extension in cases of flexor stiffness and flexion strapping program for extensor stiffness at IP joints Splinting for nerve injury will be added, which includes a knuckle bender splint if ulnar nerve injury is present and a first web spacer splint to keep the thumb in palmar abduction and extension at the CMC joint in median nerve injury	
Week 10	Stretch board exercises for IP and metacarpophalangeal (MP) joint stiffness and aggressive resistive mobilization started.	
Week 12	Desensitization exercises and activities of daily living started	

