## Procedure

### Preoperative management

The Department of Hand Surgery proforma will be used to gather baseline demographic data, which will be used to screen patients for inclusion and exclusion criteria. A preoperative clinical assessment will assess several factors that may impact the patient’s outcome following surgery. A radiograph of the affected extremity will be taken to rule out fractures. All patients will get preoperative antibiotics with tetanus prophylaxis to prevent infections. Every patient will have routine operational investigations, such as complete blood counts and serology testing, in accordance with hospital and departmental policy. Following a clear and concise explanation of the trial, written informed permission will be obtained from the participants.

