### Outcomes

Primary outcome and Secondary outcomes.

Patient-related variables:

Age.Gender.Co-morbidities.Personal habits.Preoperative mobility.Patient injury data will be sub-grouped based on the classification of Koshy et al. They will be divided into three grades based on the lacerated structures, laceration type, and repair type [3].

Primary outcome: Tang’s criteria (Total active movement) [17].

Secondary outcome:

Independent FDS function.Sensory assessment.Pinch strength.Grip strength.MCHQ (Michigan Hand Outcome Questionnaire) [18]– Functional outcome.To look for causes of motor passivity that could influence the outcome, we propose using the Kinesiophobia Causes Scale (KCS). It is observed that fear of movement, considered to be a part of an individual’s personality, could be a major limitation to motor activity. This type of behavior is described as kinesiophobia and can be documented using this scale [19].

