### Postoperative **care**

Patients in both groups will receive a dorsal thermoplastic splint on day five and start on either the active or passive mobilization program. Table 1 displays the protocol for mobilization.

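### Randomising 24 hours before surgery is earlier than the design needs and carries an avoidable risk of losses and disclosure before the arms differ on day 5

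*Protocol article*

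**What the plan says.** Under Randomization and blinding, the Protocol article states: "Randomization will be done 24 h before the surgery". Those randomised are described as already eligible: "Forty-four patients who fulfill the study’s inclusion criteria and have signed the informed consent form will be randomly assigned in a 1:1 ratio of 22" per arm. An independent resident who takes no part in treatment receives the envelope before the operation and prepares the patient for the allocated programme. The reason given is blinding before surgery.

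Eligibility rests on two injury criteria:
- Inclusion criteria: "Any of Grade 1/ 2/ 3 of the Defined Spaghetti Wrist".
- Exclusion criteria: a bedside sign, "The active movement of the digit is preserved at IP joints", followed in brackets by "Only one flexor tendon for finger or partial injury not requiring four-strand Kessler repair".

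Preoperative management describes a departmental proforma of baseline data, "which will be used to screen patients for inclusion and exclusion criteria", together with a clinical assessment and a radiograph.

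The Interventions and Surgical procedures sections give one operation for both arms. In Table 1 the day-5 splint entry is the same in both columns. Postoperative care adds: "Patients in both groups will receive a dorsal thermoplastic splint on day five and start on either the active or passive mobilization program".

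**The concern.** A trial is usually best randomised as late as practicable, once eligibility is known and just before the treatments diverge. Here the treatments diverge on day 5, yet allocation is made a day before an operation that is identical in both arms and that can still change one eligibility judgement.

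Three things can happen in that interval:
- Exploration may show a partial injury that does not need the four-strand repair. The patient is then either removed after allocation or kept without the repair that the article says every patient receives.
- The patient may withdraw, which the Study population section allows unconditionally, before receiving anything that differs between arms.
- The allocation, already acted on by the resident, may become known to the surgeon, whom the article describes as blinded.

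The stakes are precision, block balance and the security of the surgeon's blinding. The sample size includes no allowance for patients lost this way.

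**Working it through.** **1. When the allocation is needed**

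| Step | Same in both arms? | Source in the Protocol article |
|---|---|---|
| Randomisation, 24 h before surgery | Allocation now exists | Randomization and blinding |
| Operation (four-strand repair, nerve and artery repair) | Yes | Interventions; Surgical procedures |
| Day-5 splint | Yes | Table 1; Postoperative care |
| Exercises from day 5 | No: active against passive flexion | Table 1 |

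Interval from allocation to first difference: 24 h + 5 days = about 6 days, counting day 5 from surgery.

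**2. What is known before surgery**

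Preserved movement at the IP joints can be examined at the bedside, and the proforma is used for screening. Whether a partial injury needs the four-strand repair can be judged before surgery, but it is confirmed only when the tendons are seen. So one route to a change of eligibility remains open after allocation.

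**3. The plan's own sample size**

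Inputs from Sample size calculations: significance level 0.05, power 80%, effect size 0.3, m = 4 time points, correlation ρ = 0.3, stated N = 44 (22 per group). The effect size is read as Cohen's f and the test as the between-group effect in a repeated measures ANOVA. This reading returns the stated figure.

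Formula: λ = f² × N × m / (1 + (m − 1)ρ), with a noncentral F on 1 and N − 2 degrees of freedom.

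Denominator: 1 + 3 × 0.3 = 1.9.

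At N = 44: λ = 0.09 × 44 × 4 / 1.9 = 15.84 / 1.9 = 8.34, giving power 0.805. At N = 42 power is 0.786, so 44 is the smallest even total that reaches 80%. The stated figure is reproduced.

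Other readings do not return 44. The group-by-time interaction needs only 24 in total, and 0.3 read as a standardised mean difference needs 83 per arm.

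**4. Effect of losing patients before day 5**

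The article gives no rate, so the losses below are assumptions.

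| Patients lost | N left | λ | Power |
|---|---|---|---|
| 0 | 44 | 8.34 | 80.5% |
| 2 (about 5%) | 42 | 15.12 / 1.9 = 7.96 | 78.6% |
| 4 (about 10%) | 40 | 14.40 / 1.9 = 7.58 | 76.5% |

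To finish with 44 under the present timing, the trial would need 44 / 0.95 = 46.3, so 47 patients, at a 5% loss, or 44 / 0.90 = 48.9, so 49, at 10%. Randomising after repair leaves the required number at 44 as far as exclusions found at operation are concerned.

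**The case against.** The strongest reply is that the article does screen eligibility before surgery, by proforma, clinical examination and radiograph, and that the main sign in the relevant exclusion is a bedside one. This stands. A reader might infer that eligibility is settled only at operation, but the text does not support that. Surgery confirms or revises it, and probably for few patients.

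Injury grade might also be thought to be an eligibility question decided in theatre, because of the grades the article says: "They will be divided into three grades based on the lacerated structures, laceration type, and repair type". But Grades 1, 2 and 3 are all eligible, so re-grading among them excludes nobody. The argument rests on the need for the four-strand repair, not on grade.

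Nor does the article plan post-randomisation exclusions. How patients found ineligible are handled, and how analysis sets are defined, may be set out in documents that are not shown. A claim that exclusions are built in, or that patients must be dropped, goes too far.

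A claim of selection bias also goes too far. The tendon damage precedes randomisation, and exclusions judged by a surgeon blind to arm cost precision and block balance without in themselves biasing the comparison. Bias would need the allocation to become known, and the documents do not show that it does.

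Finally, the preoperative step has a stated blinding purpose. That is true, but allocation after repair serves the purpose at least as well: an allocation that does not yet exist cannot reach the surgeon during the operation.

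One might add that trauma patients may not have 24 hours before repair. The trial also recruits from the Outpatient Department, so this is a question of feasibility and not a shown contradiction.

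**Conclusion.** The point holds as a moderate, cheaply avoidable weakness of design. Allocation is made about six days before it is used, while one eligibility judgement is still open to revision, and the article gives no benefit of this timing that later allocation would not also give.

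The effect on power is modest: a fall of 1.9 points (80.5% to 78.6%) if 2 patients are lost and 4.0 points (80.5% to 76.5%) if 4 are lost. These figures assume that the losses occur at those rates, that lost patients do not contribute to the analysis, and that the sample size reading which reproduces 44 is the one intended. The true frequency is unknown. The sample size of 44 is not itself wrong on its inputs; it simply has almost no reserve. The documents do not show that the randomised comparison is already compromised.

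**What to change.** For patients still to be randomised, amend Randomization and blinding as follows:
- Keep informed consent before surgery.
- Have the same independent resident open the next sequential opaque envelope after the repair, once the operative findings confirm eligibility, and before therapy starts on day 5.
- State that all randomised patients are analysed in the arm to which they were allocated, including any randomised under the present timing.

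A patient found ineligible at operation is then recorded as screened and not randomised, so no envelope is used and the blocks stay intact. Injury grade, which the article uses for sub-grouping, is also known before allocation.

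The cost is a short amendment, notified to the ethics committee and the registry as the article already provides, and one logistic step between surgery and day 5: the resident must be told of the operative findings in time. It needs no extra staff, visits or patients, and neither the operation nor the exercise programmes change.

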**Methods:**

This study proposes a double-blind, single-center, randomized controlled trial (RCT) to compare the functional results of two rehabilitation methods following the repair of Spaghetti-wrist injuries. This includes the passive or active flexion therapy regime performed over six weeks. After fulfilling the inclusion criteria, adults aged 18–60 who have presented with spaghetti-wrist injuries will be selected. Patients will receive a comprehensive document outlining the study’s purpose, methodology, and follow-up schedule, which will be a part of the informed consent. 44 patients will be immobilized in a plaster slab and assigned equally to the passive or active flexion group. They will be assessed for primary and secondary outcomes, which include Tang’s criteria, independent digital function, sensory assessment, pinch and grip strength, and Michigan Hand Outcome Questionnaire (MCHQ), each at six and 12 weeks, six and 12 months. The study will follow the SPIRIT guidelines.

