## Methods and analysis

### Study design

The double-blind RCT will be conducted at a single tertiary referral center, comparing the functional results and complications after using two different rehabilitation programs in patients presenting to the Trauma Centre and Outpatient Department of Hand Surgery with zone-5 flexor tendon injuries. The timeline for the trial procedure is demonstrated in Fig. 1. Patients presenting from March 2023 to February 2026 fulfilling the inclusion criteria will be explained about the procedure, the risks and advantages involved, the type of subsequent rehabilitation, and evaluation by the trained instructors. All the patients will be required to provide written informed consent, and the data collected will be documented and stored for the study. The enrollment evaluation checklist and the informed consent obtained are provided in supplementary files 1 and 2 each. The protocol is prepared as recommended in the guidelines laid out in the Standard Protocol Items: Recommendations for the Intervention Trials (SPIRIT) [15].

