### Data management

A distinct number will be given to each patient, and this number will be used to record all clinical information. Perioperative assessment and examination will be the responsibility of the consultant hand surgeon and the clinical resident. The research associate will oversee the postoperative evaluation, and the associate hand surgeon will be blinded. The research associate and clinical resident will conduct routine follow-ups for a year after surgery. Using the designated computer, the Principal Investigator will oversee data entry and storage. After data gathering, an electronic database will be created and backed up. After this study, all raw data will be kept in a medical recording room for at least three years.

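### Patients and hand therapists cannot be blind under Table 1, so double-blind is the wrong label, and assessor blinding is not tied to the people who run follow-up

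*Protocol article*

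**What the plan says.** The protocol article uses the double-blind label three times: in the abstract ("This study proposes a double-blind, single-center, randomized controlled trial (RCT) to compare the functional results of two rehabilitation methods"), in Study design ("The double-blind RCT will be conducted at a single tertiary referral center") and again in the Discussion.

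The mechanism is in Randomization and blinding. Sequentially numbered opaque envelopes hold the allocation, and "an independent resident not involved in the treatment will receive the envelope"; that resident then prepares the patient for one regime or the other. The section concludes: "The surgeons, hand therapists, and data assessors tracking the patients are thus blinded by this approach", and says that this is maintained until the trial ends. Patients are not on that list.

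Table 1 sets the regimes. From day 5 the active arm flexes the fingers actively to 25%, and from day 12 to 50%, of the possible range. For the other arm, "The patient is instructed to flex the finger passively with the other hand". In weeks 3 to 5 the passive group still has its own progression. From week 6 the rows make no distinction between arms.

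Data management describes the team: "The research associate will oversee the postoperative evaluation, and the associate hand surgeon will be blinded". It adds that the research associate and the clinical resident carry out the follow-ups over the year. Outcomes names total active movement by Tang's criteria as primary but does not say who measures it.

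**The concern.** Concealing an allocation sequence and blinding a treatment are different protections. The article describes the first and claims the second. In a trial of exercise regimes, the person doing the exercise knows what it is, and so does anyone who supervises or watches it.

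The outcomes make this matter. Total active movement, grip strength and pinch strength depend on the patient's effort and on how the measurer prompts and reads. The Michigan questionnaire and the kinesiophobia scale are answered by patients who know their regime. With patients and therapists necessarily open, a credibly blinded assessor is the main protection left for the primary outcome, and that is where the role descriptions do not join up. A double-blind label would also carry into how readers grade the results.

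**Working it through.** **1. The plan's own figure.** The only design figure is the total of 44 patients. With the stated effect size of 0.3 read as Cohen's f (an assumption), m = 4 time points, correlation 0.3 and two groups, the between-groups test of a repeated-measures ANOVA has noncentrality f² × N × m / (1 + (m − 1) × ρ) = 0.09 × 44 × 4 / 1.9 = 8.34. On 1 and 42 degrees of freedom at the 5% level the power is 0.805, and 44 is the smallest even total that reaches 80%. The sample size therefore reproduces. The blinding point neither depends on it nor changes it.

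**2. What the envelope achieves.** It keeps the allocation unknown until it is opened, before surgery. Nothing described after that masks the regime.

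**3. Blinding by role.**

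| Role | What the article states | What the described design allows |
|---|---|---|
| Patients | Not listed as blinded; blinding only implied by the label | Not possible: they perform the exercises |
| Hand therapists | Blinded to the end of the trial | Not possible for any who deliver or observe therapy between day 5 and about week 5 |
| Surgeons | Blinded | Possible at operation, if the envelope stays with the resident |
| Data assessors | Blinded | Possible (step 4) |

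**4. Timing of assessment.** Outcome visits are at six weeks and three, six and 12 months. The day-5 splint specification is the same in both arms. Arm-specific instructions stop within the weeks 3 to 5 row, where the passive group moves on to full active movement, and the rows from week 6 are common. An assessor who first meets the patient at six weeks need see no arm-specific exercise or splint. What remains is disclosure by the patient, or the assessor having been present at earlier therapy.

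**5. Matching the two role descriptions.** Randomization and blinding says that data assessors are blinded but does not say who they are. Data management says who evaluates and follows up (research associate, clinical resident) but does not call them blinded. The one role it does call blinded (associate hand surgeon) receives no measurement task. Nor is it said whether the clinical resident is a different person from the resident who receives the envelope. So the article does not show that the primary outcome is measured by someone blinded, although it says that assessors are.

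**The case against.** The strongest reply has four parts.

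- **Assessor blinding is stated and workable.** This stands. A reader of Data management alone might infer that only the associate hand surgeon is blinded; the blinding section also lists surgeons and data assessors, so that inference fails.
- **The two sections are compatible.** The assessors could be the research associate and the clinical resident, and Data management never says that they are unblinded. This also stands: the sections are unmatched, not flatly contradictory. One can add that an article may leave the naming of each measurer to the full protocol. That would settle the matter if the article were silent. But it does assign roles and does name a blinded one, and the two do not meet.
- **No sentence says that therapists teach the exercises.** True. Table 1 does not name the instructor, and the resident prepares the patient. Teaching by therapists is an inference, though a strong one, since inability to attend the hand therapy program is an exclusion criterion. The point does not need it: a therapist who merely observes sessions learns the arm. If instead the resident gave all the instruction, that would sit badly with the description of the resident as outside the treatment.
- **Telling patients about both regimes is only consent disclosure.** Agreed. Patients are unblinded because they perform the regime, not because of the consent information.

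**Conclusion.** The double-blind label and the statement that hand therapists remain blinded describe a property that the design does not have. This follows from Table 1 and rests on one assumption: that therapists in the hand therapy program deliver or at least see the exercises between day 5 and about week 5. The claim is not shown to be wrong for surgeons or for data assessors; for assessors the defect is that the stated blinding is not attached to the people who do the evaluations.

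A reader might go further and infer that total active movement will be measured by unblinded staff, that the active arm will be favoured, or that the bias is some fraction of a standard deviation. The article supports none of these. It does not say who measures, and it gives no basis for the direction or size of a bias. Sample size, allocation concealment and choice of analysis are unaffected.

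**What to change.** 1. In the abstract, Study design and Discussion, replace the double-blind label with assessor-blinded, patients and therapists open. Delete hand therapists from the list of blinded roles.
2. Reconcile Randomization and blinding with Data management. State that total active movement, independent FDS function, sensation, grip and pinch are measured at all four visits by a blinded team member with no part in therapy. The associate hand surgeon would serve if that role is not involved in therapy, which the article does not say.
3. Ask patients not to reveal their regime to the assessor.
4. Report the Michigan questionnaire and the kinesiophobia scale as unblinded patient-reported outcomes.

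No regime, sample size or analysis changes. The cost is a less favourable label and some scheduling of an existing team member. The assignment should be settled before further assessments where possible, because a measurement taken unblinded cannot be repaired afterwards.
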